## 2 Introduction

Spinal cord injury can lead to paralysis of the limbs and muscles as well as a loss of function and sensation. When a person suffers an injury in the cervical (neck) region of the spinal cord, this is termed tetraplegia. Tetraplegia can lead to paralysis of all four limbs and affect the respiratory function of the patient. Poor respiratory function often leads to a patient with a cervical injury requiring mechanical ventilation and possibly a tracheostomy during the acute phase of injury [1].

Mechanical ventilation costs the local health care provider in the region of an additional £1000 per day for each patient [2]. Mechanical ventilation also reduces the patient's ability to take part in rehabilitation treatment which is a vital step of the recovery process [3]. If the time to wean from the ventilator can be reduced for this patient group this will result in a significant cost saving for the local health care provider, as well as greatly improving the patient's quality of life.

There are currently several methods available to promote weaning from mechanical ventilation. One traditional method to promote weaning is intermittent mandatory ventilation where the patient remains connected to the ventilator but is required to progressively initiate more breaths themselves. Spontaneous breathing trials (SBTs) have been shown to be a successful method to promote faster ventilator weaning than the traditional method of intermittent mandatory ventilation [4-6]. During SBTs the patient is encouraged to breathe on their own several times a day and the duration of this ventilator free time is progressively increased. As the amount of air which the patient can shift is likely to be very small at the initial stages of weaning, only short periods of time without ventilator support can be tolerated. However as the muscles regain strength the time without mechanical ventilation increases until eventually the patient becomes ventilator independent.

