Functional Electrical Stimulation (FES) is a method of stimulating the motor nerves of a muscle using a small electrical current in order to gain a functional improvement. Functional electrical stimulation when applied to the abdominal muscles is termed Abdominal Functional Electrical Stimulation (AFES). AFES has been shown to increase tidal volume (amount of air in each breath) in tetraplegia [7,8]. AFES has also been shown to be a suitable approach to improve respiratory function in chronic ventilator dependent tetraplegics without spontaneous ventilation [9]. Recent studies have shown that AFES may be a suitable method to assist ventilator weaning in the ventilator dependent tetraplegic group [10]. By making use of AFES in the acute tetraplegic population, coupled with PVFB, it may be possible to improve tidal volume to such a degree that it reduces the patient's time on a mechanical ventilator.

The total time that each patient spends on mechanical ventilation varies significantly, and there are currently no clearly defined prediction methods for weaning times [11–13]. Some studies predict that injury level, age and sex are the best indicators of the time for which a patient is likely to be ventilator dependent. Therefore a possible approach for predicting weaning time is to match subjects with a retrospective control group based on injury level, age and sex.

In summary the use of AFES in acute ventilator dependent spinal cord injured patients could support faster weaning from mechanical ventilation, with the potential to reduce health care costs and significantly improve the patient's quality of life.

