### **3 Aims**

The two main aims of this study are to evaluate the feasibility and effectiveness of abdominal Functional Electrical Stimulation to assist faster weaning from mechanical ventilation in acute ventilator dependent tetraplegic subjects.

Secondary aims of this study are (i) the evaluation of the engineering methods which have been developed to allow the synchronization of abdominal functional stimulation with a mechanical ventilator, and (ii) to investigate whether regular applications of abdominal functional electrical stimulation can improve the respiratory function of acute ventilator dependent tetraplegic patients.

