### **4 Methods**

#### **4.1 Participants**

10 ventilator dependent tetraplegic participants in the acute stage of injury will be recruited while inpatients at the Queen Elizabeth National Spinal Injuries Unit (QENSIU), Southern General Hospital, Glasgow. The participants will then be matched for injury level, age ( $\pm 5$  years) and sex against a control obtained from records of previous patients in the QENSIU. The control data will be collected by [name] and the researchers will not have access to patient notes at any point during the study.

The participants will be recruited according to the following inclusion and exclusion criteria.

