### 4.2.1 Weaning sessions

The aim of the weaning sessions is to strengthen the abdominal muscles and to provide support for ventilator free breathing.

The participant will receive AFES training once per day for a pre-determined time (see below), 4 days per week (Monday to Thursday, with rest days on Saturday and Sunday). Before the study begins and at the end of each week an assessment session (see below) will be conducted on a Friday. The participant will then spend 1 week without receiving AFES training. This cycle of 1 week with AFES training and 1 week without will give an indication of the effectiveness of AFES on the weaning progress. The total time of participation will be 8 weeks as shown in Figure 1.

[figure not shown]

Figure 1: Study timeline

AFES training sessions will continue throughout even if the patient is successfully weaned before the end of the 8 week period. All procedures will be carried out at the participant's bedside and during all procedures a clinician and the participant's nurse will be present.

The duration of AFES training will initially be 20 minutes. This will be increased to 30 minutes in week 3 and to 40 minutes during weeks 5 and 7.

During the study the participant will undergo SBTs during the weaning sessions. During these trials the participant is likely to go through four distinct phases before being successfully weaned from the ventilator as outlined in Table 1 below (adapted from [4-6]).

|                                                                                                               |                                                                                                                                                                                                                                                                                       |
|---------------------------------------------------------------------------------------------------------------|---------------------------------------------------------------------------------------------------------------------------------------------------------------------------------------------------------------------------------------------------------------------------------------|

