While the participant is still not able to breathe independently of the ventilator, Phase 1 of Table 1, AFES will be applied while the participant is connected to the ventilator. However throughout Phase 1 the ventilator support will be reduced and the weaning process will begin. As weaning progresses, Phase 2,3 and 4 of Table 1, SBTs will begin and AFES will be applied with the participant disconnected from the ventilator. While the participant is off the ventilator their oxygen saturation level ( $\text{SaPO}_2$ ) will be monitored and recorded every minute. If the participant's  $\text{SaPO}_2$  level falls below 92% the participant will be immediately reconnected to the ventilator until the  $\text{SaPO}_2$  returns to the initial value. A previous study by Girard et al. [6] suggested a  $\text{SaPO}_2$  of 88% as the point at which heterogeneous participants in an ICU should be reventilated during SBTs. However inline with current clinical procedures at the QENSIU,  $\text{SaPO}_2$  of 92% was deemed a more appropriate level at which to reventilate the participant during this study.

The participant's weaning progress will be monitored throughout the course of the study. Three measures of ventilator weaning, adapted from a previous study by Narh et al. [11], will be used to determine whether weaning has been successful: The participant is (i) *awake weaned* when they are able to breathe independently of the ventilator during the day, (ii) *short term weaned* when they do not require ventilator for 24 hours, and (iii) *long term weaned* when they have been ventilator free for 7 days. Based on previous experience most participants will not need to be reventilated after short term weaning has been achieved, although this may be compromised by comorbidities such as respiratory infection. Weaning progress is recorded in the patient notes, allowing a comparison to be made between the participants and the historic control group.

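### Historic controls are matched on injury level, age and sex only, with no condition on weaning method or admission period, so the time-to-wean comparison may mix an SBT or era effect with the AFES effect

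*Protocol*

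**What the plan says.** Section 4.1 recruits 10 participants and matches them for injury level, age (±5 years) and sex "against a control obtained from records of previous patients in the QENSIU". A named person collects the control data, and "the researchers will not have access to patient notes at any point during the study". The section gives no admission window, no condition on how a control was weaned, no list of items to abstract, and no rule for choosing when several records match. The three factors come from the Introduction, which cites them as the best predictors of ventilator dependence in some studies and proposes to "match subjects with a retrospective control group based on injury level, age and sex".

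On weaning method, the Introduction describes SBTs as "a successful method to promote faster ventilator weaning than the traditional method of intermittent mandatory ventilation". Section 4.2.1 then applies them to everyone in the study: "During the study the participant will undergo SBTs during the weaning sessions". The same section sets the oxygen saturation for reconnection at 92%, "inline with current clinical procedures at the QENSIU".

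On what the comparison is for, section 3 states: "The two main aims of this study are to evaluate the feasibility and effectiveness of abdominal Functional Electrical Stimulation". Section 4.4 makes time to wean the main outcome. Section 4.2.1 links that outcome to the controls: "Weaning progress is recorded in the patient notes, allowing a comparison to be made between the participants and the historic control group".

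**The concern.** The protocol names a feature of care that it says shortens weaning, gives it to all participants, and leaves it out of the rule for choosing controls. All three matching factors describe the patient; none describes how or when the patient was weaned. Someone following section 4.1 exactly could pick a control from any past period, weaned by any method.

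If some controls were weaned without SBTs, or under older care that differed in other ways, a shorter weaning time among participants would be partly or wholly due to that difference. Effectiveness is a main aim, and the historic controls are the only separate comparison group for the main outcome. Because the researchers have no access to the notes, they depend on what the person collecting the control data is asked to supply.

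**Working it through.** **1. No figure to reproduce.** Section 4.5 gives no alpha, power, effect size or standard deviation (SD). The target of 10 rests on patient availability. The check is a reading of the text, followed by illustrations on stated assumptions.

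**2. Participants and controls side by side.**

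| Item | Participants | Historic controls |
|---|---|---|
| Injury level, age ±5 years, sex | Known | Matched |
| Unit | QENSIU | QENSIU |
| SBTs | Yes (4.2.1) | Not stated |
| Reconnection threshold | 92%, current unit procedure (4.2.1) | Not stated |
| Calendar period | Study period | Not stated |

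**3. Can the alternate-week cycle replace the controls?** It alternates one week with AFES and one without, in the same person, and so gives some information free of era effects. But each participant has one time to wean, which can span both kinds of week. The cycle gives no with-and-without contrast on that outcome.

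**4. Structure of a possible bias.** Assume one control per participant (section 4.1 speaks of a control), that k of the 10 controls were not weaned with SBTs, that SBTs shorten weaning by D days on average, and that AFES does nothing. Then

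mean control time = T_SBT + (k/10) × D,

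and the apparent AFES effect is (k/10) × D:

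- k = 0: 0
- k = 1: 0.1 D
- k = 5: 0.5 D
- k = 10: D

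Neither k nor D is in the protocol.

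**5. What a shift of assumed size would do.** Assume 10 versus 10, unpaired, two-sided alpha 0.05, normal approximation, and no AFES effect. For a mean shift of d SDs between the groups, from SBTs or era, the chance of a significant result in favour of AFES is Φ(d × √(10/2) − 1.96):

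- d = 0.25: Φ(0.559 − 1.96) ≈ 8%
- d = 0.5: Φ(1.118 − 1.96) ≈ 20%
- d = 0.75: Φ(1.677 − 1.96) ≈ 39%
- d = 1.0: Φ(2.236 − 1.96) ≈ 61%

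With no shift it would be 2.5%. As a weaning-rate ratio R with all 20 patients weaned, Φ(ln R × √20/2 − 1.96) gives about 7%, 15% and 34% for R = 1.25, 1.5 and 2.0. All these shifts are assumptions, and the protocol specifies no such test.

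**6. Precision of a comparison that leaves out some pairs.** With m pairs and an unchanged SD of the paired differences, the 95% half-width is proportional to t(0.975, m − 1)/√m:

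| Pairs m | Factor | Wider than with 10 pairs |
|---|---|---|
| 10 | 2.262/3.162 = 0.715 | – |
| 9 | 2.306/3.000 = 0.769 | 7.5% |
| 8 | 2.365/2.828 = 0.836 | 17% |
| 7 | 2.447/2.646 = 0.925 | 29% |
| 5 | 2.776/2.236 = 1.242 | 74% |

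This measures the cost of the sensitivity comparison, not the size of the problem. It assumes a paired t interval, which the protocol does not fix, and that every patient is weaned.

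**The case against.** The strongest reply is that no confounding is shown. The statement that SBTs wean faster is general background. Nowhere does the protocol say that the unit weaned past patients by intermittent mandatory ventilation, and the tie between the 92% threshold and current unit procedures suggests that ventilator-free breathing may already be routine there. Controls come from the same unit, which limits other differences in care. All of this stands. It does not settle the matter, because current procedures say nothing about practice when the controls were treated.

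A reader might also infer that weaning method and admission date will not be recorded, or that the comparison can never be checked. The protocol supports neither. It lists no control data items, so it neither plans nor rules these out. Time to wean needs ventilation dates, so calendar time is probably recoverable. The person collecting the data works from the records and could supply the weaning method too. What holds is only that nothing requires it.

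Item lists and sensitivity reports often belong in a statistical analysis plan or data collection form, and matching on three published predictors is a defensible choice. But section 4.1 already fixes how controls are selected, and a later analysis plan cannot use an item that nobody was asked to collect.

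Finally, this is a feasibility study of 10 patients, and participants themselves begin weaning by reduced ventilator support before SBTs start, so mixed methods are to be expected among controls. That argues for a light remedy: record whether SBTs were used at all, and do not let a single exception govern the whole conclusion.

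**Conclusion.** The point holds as a minor weakness in control selection. The stated rule, followed exactly, allows controls from any period and weaned by any method, although the protocol itself treats weaning method as affecting the main outcome. The time-to-wean comparison may therefore mix an SBT or era effect with the AFES effect.

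It would be tempting to conclude that the comparison is biased in favour of AFES. The protocol does not support that: no control is shown to have been weaned without SBTs, and the bias may be zero. Its size is unknown. The k/10 relation rests on one control per participant, and the false-positive figures rest on assumed shifts and an assumed test; they illustrate sensitivity and do not estimate anything in this trial.

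**What to change.** Add to section 4.1, in substance:

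- The person collecting the control data records, for each control, whether SBTs were used in weaning and the date of admission.
- Where more than one record meets the three matching criteria, an SBT-weaned record is preferred, and then the most recent.
- If some controls were not weaned with SBTs, their number is reported, a sensitivity comparison without those pairs is shown beside the full one, and the effectiveness statement is qualified accordingly.

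The match is not loosened, no record leaves the pool, and the researchers still need no access to the notes. The preference rule helps only where several records match equally, and the protocol does not show how often that will happen.

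The cost is two extra abstracted items per control, a less precise sensitivity comparison (by the margins tabulated above, depending on how many pairs drop out), and possibly a more cautious conclusion.

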#### **Inclusion criteria:**

- Men or women over 16 years of age;
- Acute spinal cord injury (Patients with a new spinal cord injury);
- Reduced respiratory function requiring mechanical ventilation;
- Good visual response to surface abdominal stimulation, suggesting that lower motor neurons are intact.

#### **Exclusion criteria:**

- Under 16 years of age;
- Female subjects who are pregnant;
- Significant history of autonomic dysreflexia;
- No visual response to surface abdominal stimulation, suggesting that lower motor neurons are not intact.

#### **4.2 Experimental Procedures**

Each participant will take part in daily AFES training sessions (5 times per week) during alternative weeks. Progress will be monitored during weekly assessment sessions. The total duration of participation is 8 weeks.

### 4.2.1 Weaning sessions

The aim of the weaning sessions is to strengthen the abdominal muscles and to provide support for ventilator free breathing.

The participant will receive AFES training once per day for a pre-determined time (see below), 4 days per week (Monday to Thursday, with rest days on Saturday and Sunday). Before the study begins and at the end of each week an assessment session (see below) will be conducted on a Friday. The participant will then spend 1 week without receiving AFES training. This cycle of 1 week with AFES training and 1 week without will give an indication of the effectiveness of AFES on the weaning progress. The total time of participation will be 8 weeks as shown in Figure 1.

[figure not shown]

Figure 1: Study timeline

AFES training sessions will continue throughout even if the patient is successfully weaned before the end of the 8 week period. All procedures will be carried out at the participant's bedside and during all procedures a clinician and the participant's nurse will be present.

The duration of AFES training will initially be 20 minutes. This will be increased to 30 minutes in week 3 and to 40 minutes during weeks 5 and 7.

During the study the participant will undergo SBTs during the weaning sessions. During these trials the participant is likely to go through four distinct phases before being successfully weaned from the ventilator as outlined in Table 1 below (adapted from [4-6]).

|                                                                                                               |                                                                                                                                                                                                                                                                                       |
|---------------------------------------------------------------------------------------------------------------|---------------------------------------------------------------------------------------------------------------------------------------------------------------------------------------------------------------------------------------------------------------------------------------|
| 1. Participant unable to breathe independently of ventilator but with gradually decreasing ventilator support | Participant will not be able to breathe independently of the ventilator. Therefore all procedures will be carried out with the participant connected to the ventilator.                                                                                                               |
| 2. Participant taken off ventilator for the first time and SBTs begin                                         | Participant will only be able to breathe independently of the ventilator for a short period of time before SaPO 2 falls below 92%. It is unlikely that the participant will be able to actively participate or follow instructions. All breaths will be at vital capacity. |
| 3. Participant becomes more accustomed to breathing without ventilator support for longer periods of time     | Duration of time off the ventilator increases before SaPO 2 falls to 92%. However breaths are still at vital capacity until respiratory function begins to improve.                                                                                                        |
| 4. Participant can actively participate while off ventilator                                                  | Participant can spend the whole session disconnected from the ventilator. Respiratory                                                                                                                                                                                                 |

|  |                                                                                                                                                                        |
|--|------------------------------------------------------------------------------------------------------------------------------------------------------------------------|
|  | function improves to level where tidal volume of normal breath is below vital capacity. Participant can actively take deeper breaths to vital capacity when requested. |
|--|------------------------------------------------------------------------------------------------------------------------------------------------------------------------|

Table 1: Phases of weaning.

While the participant is still not able to breathe independently of the ventilator, Phase 1 of Table 1, AFES will be applied while the participant is connected to the ventilator. However throughout Phase 1 the ventilator support will be reduced and the weaning process will begin. As weaning progresses, Phase 2,3 and 4 of Table 1, SBTs will begin and AFES will be applied with the participant disconnected from the ventilator. While the participant is off the ventilator their oxygen saturation level ( $\text{SaPO}_2$ ) will be monitored and recorded every minute. If the participant's  $\text{SaPO}_2$  level falls below 92% the participant will be immediately reconnected to the ventilator until the  $\text{SaPO}_2$  returns to the initial value. A previous study by Girard et al. [6] suggested a  $\text{SaPO}_2$  of 88% as the point at which heterogeneous participants in an ICU should be reventilated during SBTs. However inline with current clinical procedures at the QENSIU,  $\text{SaPO}_2$  of 92% was deemed a more appropriate level at which to reventilate the participant during this study.

The participant's weaning progress will be monitored throughout the course of the study. Three measures of ventilator weaning, adapted from a previous study by Narh et al. [11], will be used to determine whether weaning has been successful: The participant is (i) *awake weaned* when they are able to breathe independently of the ventilator during the day, (ii) *short term weaned* when they do not require ventilator for 24 hours, and (iii) *long term weaned* when they have been ventilator free for 7 days. Based on previous experience most participants will not need to be reventilated after short term weaning has been achieved, although this may be compromised by comorbidities such as respiratory infection. Weaning progress is recorded in the patient notes, allowing a comparison to be made between the participants and the historic control group.

